### Structural brain adaptations using MRI

Structural whole-brain networks changes will be researched by applying different MRI techniques during pre, mid, and post-test assessment. MRI-assessment is part of the clinical investigation of WP1. An MRI scan will be conducted to gather an anatomical scan comprising different sequences on a 3-Tesla MRI-unit. A 30-minute protocol will be followed, compiled out of scout images, 3D T1-weighted spin-echo images, diffusion-weighted imaging HARDI and an optional 3D MAGIC. These measurements will consequently be used to determine whole-brain networks based on the cortical and subcortical regions of interest [23][24]. Regions of interest will include the primary motor cortex, primary somatosensory cortex, premotor cortexes, supplementary motor area, corpus callosum, basal ganglia, thalamus and cerebellum as they are responsible for motor control and balance.

## f) Any procedures for the replacement of subjects

Not applicable.

## h) Definition of completion of the clinical investigation

The clinical investigation will be considered as terminated when the proposed sample size is tested and is defined as the last visit of the last subject.

## 6.2. Investigation device(s) and comparator(s)

### a) Description of the exposure to the investigational device

20 subjects are asked to do their rehabilitation process with the LUNARIS® and then to perform their daily activities with the LUNARIS® during a period of 6 months in total. They are also asked to perform the above mentioned activities with the LUNARIS® during 2 experimental sessions.

### b) List of any other medical device or medication to be used

20 subjects are asked to do their rehabilitation process with an usual rigid passive foot (SACH®) and then to perform their daily activities with the most suited prosthesis for them during a period of 6 months in total. They are also asked to perform the above mentioned activities with the most suited prosthesis for them during 2 experimental sessions.

### c) Number of investigational devices to be used

The LUNARIS®, already extensively described in this document and in the investigator brochure, is the only investigational device that will be used.

## 6.3. Subjects

### a) Inclusion criteria for subject selection

- Age: 25 - 65 years
- Gender: men and women
- Level of amputation: unilateral transtibial
- Medicare Functional Classification Level: K3-K4

### b) Exclusion criteria for subject selection

- Having metal implants
- Bilateral or additional upper-limb amputation
- Diabetic cause of amputation
- Neurological disorders
- Excessive stump pains and wounds

### c) Criteria and procedures for subject withdrawal or lost to follow-up

Participants can withdraw at any time without reason from the experiment. In case of subjects drop-out is not met, additional subjects will be recruited via the same rehabilitation centres and orthopaedics departments of hospitals until the sample size is obtained (40 lower-limb amputees and 20 able-bodied subjects).

### d) Point of enrolment

Participants will be recruited via rehabilitation centres and orthopaedics departments of hospitals such as CHU Brugmann Queen Astrid, UZ Leuven campus Pellenberg, Ghent University Hospital, Revarte and Centre de Traumatologie et de Réadaptation. All participants will be providing written and oral information about the experimental protocol, potential risks and benefits before giving informed consent to participate in the study.

### e) Point of randomization

Non-randomized.

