### c) Scientific justification and clinical relevance for effect sizes

The primary endpoint of the clinical trial is the distance covered during the 6-minutes' walk test. The sample size was calculated based on a study comparing passive and quasi-passive prosthetic ankles which found an effect size Cohens'  $f = 0.318$  on distance covered during the 6-minutes' walk test [4]. A total of 40 participants with a lower limb amputation is required and will be allocated to one of the two prosthetic groups. These individuals will be stratified by age (2 strata:  $< 45$  years,  $\geq 45$  years, block size = 4) to control for age-related cognitive deterioration. A matched control-group of 20 able-bodied individuals will be included to enable comparison. The required number of 40 participants with amputation is based on a sample size calculation for an analysis of variance using G\*Power (version 3.1.9.4) envisaging 10% drop-out. Values used for this calculation were medium expected effect size  $f = 0.318$ , power = 0.80,  $\alpha = 0.05$ , the number of groups = 3 and the number of measurements set at 2 with a correlation between measurements of 0.75.

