## 6. Design of the clinical investigation

### 6.1. General

#### a) Description of the design type of clinical investigation to be performed

This cohort study includes three groups.

- 20 lower-limb amputees who are going to do their rehabilitation and perform daily activities with a new articulated ankle foot prosthesis: the LUNARIS®.
- 20 lower-limb amputees who are going to do their rehabilitation and perform daily activities with a conventional prosthetic ankle: the SACH® followed by the most suited prosthesis for them.
- 20 able-bodied subjects which will be used as a control group.

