##### Protocol:

Figure 2 provides a visualisation of the investigation workflow.

[figure not shown]

Figure 2: Overview clinical trial. MRI: Magnetic Resonance Imaging, PEQ: Prosthetic Evaluation Questionnaire, ADL: Activities of Daily Living

The clinical investigation will comprise 4 test days for participants with a lower limb amputation and 2 days for the control group of able-bodied individuals.

The able-bodied individuals will undergo an MRI-scan at the University hospital Brussels (dpt. Radiology and Magnetic Resonance) and then perform functional performance tests.

Participants with a lower limb amputation will start the clinical investigation upon the start of their rehabilitation. At week 0, when initiating the rehabilitation, participants will undergo a baseline MRI-scan at the University hospital Brussels (dpt. Radiology and Magnetic Resonance). Then, they will be allocated to the one of the treatment arms (LUNARIS® or the SACH® foot) and will conduct their rehabilitation to learn walking with a prosthesis. At the end of the rehabilitation, after 12 weeks, participants will perform baseline functional performance tests, fill out the prosthetic evaluation questionnaire (PEQ) measuring quality of life [11] and fill out the Mini-Mental State Examination to account for cognitive impairments and onset of Alzheimer's Disease [12]. Between weeks 12 and 24 of the clinical investigation (i.e. intervention period), participants will perform their daily activities with the allocated prosthesis. During this 12-week period, trying out new prosthetic devices will be allowed within the group of individuals wearing the SACH® foot as this is considered the usual care. At the end of this period (after week 24), post-test assessment will take place and participants will undergo the same MRI and functional performance tests as during the baseline assessments to evaluate the changes that occurred. Additionally, the participant will be asked to fill out the Quebec User Evaluation of Satisfaction with assistive Technology (QUEST 2.0) to assess prosthetic satisfaction [25-27]. The 12-week intervention period is chosen based on a study examining the effect of 12 weeks balance training in healthy and older adults on neuroplasticity and on the accommodation time to walking with a new prosthesis [13][14][15].

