### c) Any known or foreseeable factors that can compromise the outcome of the clinical investigation or the interpretation of results

There are no known or foreseeable factors that can comprise the outcome. Subjects are asked to behave as normal as possible before, during and after the experiment concerning the amount of physical activity and medication intake.

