### e) Sample size calculation and justification

The primary endpoint of the clinical trial is the distance covered during the 6-minutes' walk test. The sample size was calculated based on a study comparing passive and quasi-passive prosthetic ankles which found an effect size Cohens'  $f = 0.318$  on distance covered during the 6-minutes' walk test [4]. A total of 40 participants with a lower limb amputation is required and will be allocated to one of the two prosthetic groups. These individuals will be stratified by age (2 strata:  $< 45$  years,  $\geq 45$  years, block size = 4) to control for age-related cognitive deterioration. A matched control-group of 20 able-bodied individuals will be included to enable comparison. The required number of 40 participants with amputation is based on a sample size calculation for an analysis of variance using G\*Power (version 3.1.9.4) envisaging 10% drop-out. Values used for this calculation were medium expected effect size  $f = 0.318$ , power = 0.80,  $\alpha = 0.05$ , the number of groups = 3 and the number of measurements set at 2 with a correlation between measurements of 0.75.

- f) The rationale for the number of procedures to be performed by a single user as part of the learning curves

A baseline experiment with a conventional prosthetic ankle used in rehabilitation is required to observe any similarities or differences in outcomes with the LUNARIS®. Moreover, a baseline experiment with able-bodied subjects is required to observe any similarities or differences in outcomes with the LUNARIS®. Therefore, each lower-limb amputee is asked to schedule four appointments and each able-bodied subject is asked to schedule two appointments to run through the whole experiment.

- g) Pass / Fail criteria to be applied to the results of the clinical investigation

Not applicable.

- h) The provision for an interim analysis

Not applicable.

- i) Management of bias

All appointments for the MRI will take place at UZ Brussel to avoid any bias due to a different MRI scanner. All appointments for functional performance testing will take place at Axiles Bionics to avoid any bias due to different slopes or staircases between subjects and between sessions.

- j) Management of potential confounding factors

Not applicable.

- k) Description of procedures for multiplicity control and adjustment of error probabilities

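### The protocol declares allocation non-randomised but describes age-stratified blocks of 4, and its confounding provisions contradict each other, so the H1 device comparison is not protected from selection bias

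*Protocol*

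**What the plan says.** **How the foot is assigned.**

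- Section 6.3 e), on the point of randomisation: "Non-randomized".
- Section 6.1 a): "This cohort study includes three groups".
- Section 7 e), repeated in 5 c): "A total of 40 participants with a lower limb amputation is required and will be allocated to one of the two prosthetic groups". It goes on: "These individuals will be stratified by age", with a cut at 45 years and "block size = 4) to control for age-related cognitive deterioration".
- Section 6.1 d), under Protocol: after the week-0 MRI, "they will be allocated to the one of the treatment arms".

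**How confounding is handled.**

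- Section 7 j), headed "Management of potential confounding factors", is marked as not applicable.
- Section 6.4 c): "There are no known or foreseeable factors that can comprise the outcome". Section 6.4 d) relies on the eligibility criteria as the control.
- Sections 6.1 b) and 7 i) limit bias control to using one scanner and one test site.
- Section 7 b) nevertheless plans adjustment. For the functional tests it lists age, time since amputation, side, level, time on a prosthesis and previous prosthesis. For the brain outcomes it gives a longer list, which adds sex, cognitive score and education, and it speaks of controlling for confounders.

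**The concern.** The study itself decides who receives the LUNARIS, so how it decides is the main safeguard of the primary comparison. A block size has a function only in an allocation schedule, normally a random one. Sections 5 c) and 7 e) therefore point one way, and 6.1 a) and 6.3 e) the other. A site could not tell from this text how the next participant is to be assigned.

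H1 claims that LUNARIS users will walk further in 6 minutes, with 35 m as the threshold of relevance. If assignment is not random, a week-24 difference mixes the effect of the foot with differences between the people who received it. The section meant to deal with this is left empty, and it disagrees with the analysis section.

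**Working it through.** The point rests on text. The protocol gives no figure for imbalance between the arms, so there is none to reproduce. The planned 40 amputees (20 per arm) do not change with the way the foot is assigned.

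**Step 1. Is the assignment method consistent?** No. Sections 6.1 a) and 6.3 e) cannot stand beside an age-stratified blocked allocation in 5 c) and 7 e). If allocation is random, 6.1 a) and 6.3 e) misstate the design. If it is not, the block size has no stated function, and neither the mechanism nor a reason for not randomising is given. Either way the text must change.

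**Step 2. Is the handling of confounding consistent?** No. Section 7 j) says the matter does not arise, while 7 b) plans adjustment in both analyses.

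**Step 3. Would the adjustment in 7 b) protect H1 under non-random assignment?**

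| Item | What the protocol fixes | Consequence |
|---|---|---|
| Amputation level | 6.3 a) admits only unilateral transtibial | Constant, adjusts for nothing |
| Time on a prosthesis, previous prosthesis | 6.1 d): entry at the start of rehabilitation, when walking with a prosthesis is learned | Little variation to be expected |
| K-level | 6.3 a) admits K3 and K4 | Not in the functional-test list |
| Sex | In the brain list in 7 b) | Not in the functional-test list |
| 6-minute walk before allocation | 6.1 d) and 6.4 a): first walk at week 12 | Does not exist |

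Age, time since amputation and side remain as the useful covariates. The week-12 walk is taken after 12 weeks on the allocated foot. Adjusting for it as though it preceded treatment would adjust for something that the device may already have changed.

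**Step 4. What could an uncorrected imbalance do?** This is an illustration. The imbalance *b*, in SD units of the outcome, is assumed because the documents give none. Take no true device effect, no covariate adjustment and a two-sided 5% test with *n* per arm:

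SE = √(2/*n*); rejection rate = 1 − Φ(1.96 − *b*/SE) + Φ(−1.96 − *b*/SE).

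For *n* = 20, SE = √0.10 = 0.316. With *b* = 0.2, *b*/SE = 0.632, and the rate is 1 − Φ(1.328) + Φ(−2.592) ≈ 0.092 + 0.005 = 0.097. The 10% drop-out in 7 e) gives *n* = 20 × 0.9 = 18.

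| Assumed imbalance (SD) | 20 per arm | 18 per arm |
|---|---|---|
| 0 | 5.0% | 5.0% |
| 0.1 | 6.2% | 6.0% |
| 0.2 | 9.7% | 9.2% |
| 0.3 | 15.8% | 14.7% |
| 0.5 | 35.3% | 32.3% |

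The table shows sensitivity only. It does not estimate the bias in this trial, and any useful adjustment would lower the figures.

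**The case against.** Much can fairly be said for the protocol, and it rules out several stronger readings.

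- *That confounding is ignored.* It is not. Section 7 b) plans adjustment and 6.4 d) names the eligibility criteria as a control. The fault is that 7 j) contradicts 7 b) and that the functional-test list is weak.
- *That staff will steer fitter patients to the LUNARIS.* Nothing in the protocol says who chooses. It says only that participants are allocated. The defect is that no mechanism is stated.
- *That randomisation is forgone for no reason.* The documents show only that no reason is stated.
- *That the causal claim for the MRI part fails too.* The causal wording in 7 b) concerns brain structure and performance, not the device and the brain. Randomising the foot would not establish that link. A pre-allocation scan also exists at week 0.
- *That the bias can be put in metres against the 35 m threshold.* That would need the difference in walking distance between K3 and K4 and the imbalance in K-level. The protocol gives neither.

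Two further objections stand in part. A prosthetic walk test at week 0 may not be feasible in people still learning to walk, and randomisation would not supply one. That makes sound assignment more important. Nor would randomisation alone attribute a week-24 difference to the foot, because the SACH group may change devices between weeks 12 and 24, and 7 m) excludes drop-outs. It would remove selection at assignment and nothing more.

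**Conclusion.** The point stands and needs correction before the trial relies on H1. Two contradictions are plain in the text: non-randomised cohort against age-stratified blocks of 4, and confounding not applicable against planned adjustment. The first leaves assignment undefined. Under the non-random reading, the week-24 comparison is open to selection bias that the listed covariates cannot be relied on to remove, and there is no pre-allocation value of the primary endpoint with which to detect it. The documents do not allow the size of that bias to be estimated; the error rates above depend wholly on the assumed imbalance and on no adjustment.

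The conclusion assumes that a block size signals an allocation schedule. The protocol does not call that schedule random. If random allocation is what is meant, the defect is one of wording in 6.1 a), 6.3 e) and 7 j).

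**What to change.** **Preferred.**

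- Amend 6.3 e) to 1:1 random allocation of the amputees at week 0, after the baseline MRI, from a concealed computer-generated list in blocks within the two age strata (<45, ≥45 years).
- Correct the cohort label in 6.1 a).
- Include the age stratum in the primary model.
- Replace the entry in 7 j) with a pre-allocation adjustment set and reconcile it with 7 b): drop amputation level, add K-level, and do not treat the week-12 walk as a pre-treatment covariate.
- Keep the list away from those who enrol. The foot is visible, so the last assignment in a known block of 4 can be deduced; varying the block size would reduce this.

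**If randomisation is not possible.** Delete the block wording, justify the non-randomised design, state the assignment mechanism and the pre-allocation confounders in 7 j), and limit the H1 device conclusions to association.

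**Cost.** One allocation list and one amendment, with the ethics approval and authority no-objection steps in section 9. The sample size is unchanged, and the strata, blocks and allocation point are already planned. The downside is that clinicians lose the choice of foot at week 0.

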### f) Total expected duration of the clinical investigation

We expect to start the clinical investigation in September 2023. It will last at least for 2 years.

### g) Expected duration of each subject's participation

Each subject is asked to schedule four appointments. The total duration of the clinical investigation for each subject is 24 weeks.

### h) Number of subjects required to be included in the clinical investigation

We want to include 40 lower-limb amputees and 20 able-bodied subjects. Several rehabilitation centres and orthopaedics departments of hospitals were already contacted and agreed to participate in this study by providing us lower-limb amputees.

### i) Estimated time needed to select this number (enrolment period)

Enrolment will be performed before and during the experiment. We expect that it will take less than 2 years to gather enough subjects for this clinical investigation.

### j) Relationship of investigation population to target population

The investigation population could be the future target population.

### k) Information on vulnerable, pregnant, and breastfeeding population

Not applicable.

## 6.4. Procedures

### a) Description of all clinical investigation-related procedures that subjects undergo during the clinical investigation

*Lower-limb amputees:*

There are three measurement moments for lower-limb amputees which will be divided into four days.

**Day 1:** the subject will be expected at the radiology department at UZ Brussel. Here, a non-invasive brain scan will be taken under the supervision of [name]. [name] (department head of Radiology). This measurement moment will take approximately 60 minutes.

**After 12 weeks:** the subject will be expected at Axiles Bionics for a series of non-invasive tests. This measurement moment will take approximately 120 minutes.

**After 24 weeks:** this measurement moment will be divided into two days. The subject will be expected on day 1 at the radiology department at UZ Brussel. Here, the same brain scan will be taken as described in measurement moment 1. This measurement moment will take about 60 minutes. On day 2, the subject will be expected at Axiles Bionics for a series of non-invasive tests as described in measurement moment 2. This measurement moment will take about 120 minutes.

### *Able-bodied subjects:*

There is only one measurement moment for able-bodied subjects which will be divided into two days.

**Day 1:** the subject will be expected at the radiology department at UZ Brussel. Here, a non-invasive brain scan will be taken under the supervision of [name]. [name] (department head of Radiology). This measurement moment will take approximately 60 minutes.

**Day 2:** the subject will be expected at Axiles Bionics for a series of non-invasive tests. This measurement moment will take approximately 60 minutes.

### b) Description of those activities performed by sponsor representative

The sponsor is responsible for the execution of the experimental tasks, data gathering and analyses.

### c) Any known or foreseeable factors that can compromise the outcome of the clinical investigation or the interpretation of results

There are no known or foreseeable factors that can comprise the outcome. Subjects are asked to behave as normal as possible before, during and after the experiment concerning the amount of physical activity and medication intake.

### d) The methods for addressing these factors in the clinical investigation

Specific inclusion and exclusion criteria are applied before enrolment to counteract as possible factors that can compromise the outcome.

### e) The follow-up period during the clinical investigation

The principal investigator and co-investigators are available during the entire duration of the experiment of each subject. Follow-up is provided for each subject during their participation via direct appointments or via other channels such as email or telephone calls.

- f) Address what specific medical care is appropriate to be provided for the subjects after the clinical investigation has been completed

There is no follow-up plan considered since subjects are doing the rehabilitation process as usual and perform their daily activities with the investigational device or with the most suited prosthesis for them. Subjects can contact our department after and during the experiment for any further questions.

- g) Address recommended follow-up for the subjects after the clinical investigation has been completed

There is no follow-up plan considered since subjects are doing the rehabilitation process as usual and perform their daily activities with the investigational device or with the most suited prosthesis for them. Subjects can contact our department after and during the experiment for any further questions.

- h) Address the final disposition or potential future use of samples obtained from subjects

All anonymized data will be stored for up to 10 years as recommended by the VUB.

